### Statistical analysis plan

All statistical analyses will be analyzed using Stata, version 16.0 (StataCorp, College Station, Texas). The significant level was tested at *P* value <0.05 based on hypotheses of two-tailed tests. Missing values will be handled with a multiple imputation method. Descriptive statistics will be analyzed and presented as number (%), mean (SD), or median (min–max) as appropriate.

Item analysis will be assessed descriptively and summarized along with the normality of score distribution, including skewness and kurtosis tests. The Kaiser-Meyer-Olkin measure and Bartlett test of sphericity will be tested to ensure the appropriate scale factor analysis of the measurement scales. For preplanned EFA, we will employ a principle factor extraction method, with the obliquely rotated using the Promax criterion. Eigenvalues with a criterion of >1.0 will be considered as the number of factors retained. The unidimensional set or subscales will be tested using a non-parametric IRT. The item characteristics curve analysis will be visualized to describe the characteristics of individual items within the particular scale. During the follow-up period, we will perform a CFA with a maximum likelihood estimation to reaffirm the scale structure. Specific fit indices will be tested, including the comparative-fit index (>0.900), non-normed fit index or Tucker-Lewis index (<0.900), standardized root mean squared residual (<0.100), and root mean square error of approximation (<0.100).

To assess the psychometric properties, we will test the convergent validity of the sets of PROs-CP measurement scales using Pearson’s or Spearman’s correlation coefficients as appropriate. The 95% confidence intervals (CIs) of correlation coefficient statistics will be estimated using the bootstrap resampling method. A know-group or discriminant validity will be assessed based on pruritus intensity—visual analog scale as follows: mild (0.1–2.9), moderate (3.0–6.9), severe (7.0–8.9), and very severe (9.0–10.0) [2]. Internal consistency reliability will be tested using Cronbach’s α and McDonald’s ω coefficients with 95% CIs (values of >0.7 indicate acceptable reliability). Scale reproducibility will be tested using intraclass correlation coefficients. The kappa (κ) coefficient of the agreement and area under the receiver operating characteristic curve will be used to assess the optimal cut-off severity or burden score to establish banding of measurement scales with anchor-based questions.

All interviews’ audio recordings will be transcribed verbatim. Deidentified transcript data from the in-depth interview process will be uploaded, coded, and refined by professional experts in qualitative research (RA, CP, and YR). For qualitative analysis, we will employ content analysis to summarize the interview information and assess the consistency of coding and refinement concepts that capture patient views and experiences of chronic pruritus. A thematic approach based on grounded theory techniques will be used to analyze and identify patterns or themes (subthemes) from patient perspective information [35, 36]. Furthermore, we also plan to qualitatively synthesize among subgroups with severe or very severe pruritus intensity to reflect the impacts of chronic pruritus that are most important to patients with high-burden disease activity. The saturation of concept findings from qualitative interviews will be reaffirmed using saturation tables to verify and track the concepts of how pruritus affected the patient’s life.

For longitudinal follow-up at one year, differences between groups (predefined based on pruritus intensity as mild, moderate, severe, and very severe) will be tested using Fisher’s exact test for categorical data and analysis of covariance or Kruskal-Wallis test for continuous data. The multivariable Tobit, modified Poisson, and ordinal logistic regression analysis will be analyzed to explain the relationship between the degree of pruritus intensity and long-term health outcomes. The effect estimates of the findings will be reported as β coefficients, risk ratios, and common odds ratios, respectively, corresponding with CIs.

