### Study I: PROs measure development, translation, and psychometric validation

We will follow the established methods and consecutive phases for scale development to create multidimensional scales [8, 28]. The series of phases for scale development are illustrated in Fig 2. In brief, phase I—item generation will review the literature regarding general- and pruritus-specific disease activity control and treatment satisfaction. The subsample of 30 patients with chronic pruritus will be interviewed using structured and non-structured in-depth interviews to provide and reflect the perspectives regarding pruritus-specific disease control and their satisfaction with treatment care. In phase II, we will generate pilot questionnaires based on literature review and patient perspectives. The pilot questionnaires will then be reviewed by a panel of experts and patients to modify and verify in terms of face and content validity. In phase III, we will refine the particular questionnaire via an optimal sample to establish scale dimensionality using exploratory factor analysis (EFA, based on the rule of thumbs, 5–15 patients per question) and non-parametric item response theory (IRT) [8, 28, 29]. Lastly, in phase IV, we will perform an initial psychometric analysis to verify the validity and reliability of the final scale. For scale stability, a random subsample will be asked to complete the particular scale twice, within a 60–120 min interval.

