Two independent bilingual native English speakers will independently blind-translate the synthesized measurement scales back into English. For the back-translation process, no translators had any medical health/dermatology background or acknowledged information regarding the particular original English version. To ensure that the translated version reflects the content of the original version, the content validity of the back-translation questionnaire will be reviewed and addressed. After that, both versions of the backward translations will be compared and reconciled with the original English version. To ensure equivalence between the original and translated Thai versions, conceptual equivalence (ensuring that words can hold the same conceptual meaning), item equivalence (individual items have the same relevance), and semantic equivalence (meaning of the items is the same in both version) will be employed. In the same manner as pilot testing and refinement of the scale development, a panel of experts and patients will review and refine the preliminary translated scales. Next, the EFA, non-parametric IRT, and initially psychometric analysis will be conducted to establish the validity, reliability, and scale stability (reproducibility) of the translated scales Thai version (i.e., ItchyQoL, PUSH-D, and TAS-20).

To track the treatment responses, the responsiveness of the pruritus-specific disease activity control (planned to develop through this study) and pruritus-specific HRQoL (using the ItchyQoL) in terms of the MCID will also be defined and established among patients with chronic pruritus. For scale interpretability in terms of MCID, we will incorporate both anchor-based and distributional criterion approaches using the change scales of disease activity and ItchyQoL at week 12 of follow-up [31–33].

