### Sample size estimation

Although we plan to include all eligible patients in this open longitudinal study, a pre-specified sample size for scale development and validation of the PRO-CP measurement tool was estimated. As such, sample size consideration for this study will be calculated based on two parameters. Firstly, we use a sample-to-item ratio (5–15 patients per question for both the EFA and CFA approach) to address a scale structure for factor analysis [8, 28, 29]. Secondly, a fair correlation coefficient statistic (>0.30) with anchor-based questions was used to establish convergent validity [34]. Regarding a power of 80% and 0.05 type I error, a minimum target of 396 patients with chronic pruritus is needed for this study cohort to account for missing responses of 20% during the cohort follow-up.

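### An eigenvalue cut-off of 1.0 applied to principal-factor extraction can drop real factors when subscales are short, loadings moderate and factors correlated

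*Protocol article*

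**What the plan says.** The Statistical analysis plan section of the protocol article fixes the extraction and the rotation: "For preplanned EFA, we will employ a principle factor extraction method, with the obliquely rotated using the Promax criterion". The next sentence gives the rule for the number of factors: "Eigenvalues with a criterion of >1.0 will be considered as the number of factors retained". No other rule is named, and the text does not say that the eigenvalues are read from the unreduced correlation matrix.

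The section on Study I gives this step its purpose for the new multidimensional scales, "to establish scale dimensionality using exploratory factor analysis (EFA, based on the rule of thumbs, 5–15 patients per question". It extends the step to the Thai ItchyQoL, PUSH-D and TAS-20: "Next, the EFA, non-parametric IRT, and initially psychometric analysis will be conducted". Non-parametric item response theory (IRT) then tests the resulting sets or subscales. A confirmatory factor analysis (CFA) during follow-up is meant to confirm the structure already found.

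**The concern.** The cut-off and the extraction method do not belong together. In a full correlation matrix each item contributes variance 1, so the eigenvalues average 1, and a factor above 1 explains more than one item's worth. Principal-factor extraction replaces the diagonal by communalities. Every eigenvalue then falls, and 1 is no longer the natural reference. Correlated factors, which an oblique rotation allows for, move variance into the first eigenvalue and lower the later ones further.

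The number of factors determines which items form a subscale, which sets go to IRT, what the omega coefficients describe and which CFA model is fitted. Psychometric validation is the first primary objective. For the two new multidimensional scales (disease control and treatment satisfaction), no earlier structure exists against which a merged dimension would stand out.

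**Working it through.** **Inputs from the protocol article.** Principal-factor extraction, Promax, cut-off 1.0; target 396 with 20% missing responses (Sample size estimation); TAS-20 with 20 items and PUSH-D with 17 (Table 2). The plan states no number of factors, so it has no figure of its own to reproduce.

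**Assumptions.** The article gives no factor structure, loadings or factor correlations, so the following are assumed:
- simple structure with equal loadings of 0.6 or 0.7 and factor correlation 0.5 unless stated;
- five-category items (cut at −1.5, −0.5, 0.5 and 1.5 SD in the final run);
- n = 396 × 0.8 = 317;
- 22 items for ItchyQoL, inferred from its maximum of 110 at 5 points per item.

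**Population check.** For equal blocks of k items with loading λ, factor correlation φ and diagonal entry d, every eigenvalue after the first that belongs to a true factor is

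d + (k − 1)λ² − kφλ².

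Three factors of 4 items, λ = 0.7, φ = 0.5 (λ² = 0.49, φλ² = 0.245):
- full matrix, d = 1: 1 + 1.47 − 0.98 = 1.49, so three factors are kept;
- reduced matrix, d = squared multiple correlation = 0.375: 0.375 + 1.47 − 0.98 = 0.87, so one factor is kept;
- reduced matrix with the true communality, d = 0.49: 0.98, still below 1.

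Here the rule fails in the population, so a larger sample does not help.

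Four factors of 5 items, λ = 0.7, φ = 0.5, d = 0.399: 0.399 + 1.96 − 1.225 = 1.13. This is above 1, so losses in this design come from sampling spread among the three later eigenvalues and from the weaker correlations of coarse items.

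**Simulation.** Squared multiple correlations were placed on the diagonal. Eigenvalues above 1 were counted and compared with parallel analysis on the same reduced matrix (95th percentile from random data of the same n and item count). The final run used 500 samples per structure. Ranges are over repeated simulations at n = 317.

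| Assumed structure | Last true eigenvalue, full | Reduced | Too few factors kept |
|---|---|---|---|
| 4 × 5 items, 0.7 | 1.73 | 1.13 | 79–84% |
| 3 × 4 items, 0.7 | 1.49 | 0.87 | 99.7–100% |
| 7/9/6 items, 0.6 | 1.79 | 1.07 | 35–41% |
| 7/9/6 items, 0.7 | 2.07 | 1.49 | 0% |
| 7/5/8 items, 0.6 | 1.64 | 0.91 | 82–85% |
| 6/6/5 items, 0.6 | 1.59 | 0.86 | 98–99% |
| 6/6/5 items, 0.7 | 1.80 | 1.20 | 22–23% |
| 3 × 4 items, 0.7, factor correlation 0.3 | 1.88 | 1.25 | 33–34% |

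The planned rule never kept too many factors. Parallel analysis was right in 97–100% of samples. At n = 396 the first four rows give 81%, 100%, 41% and 0%. Coarse categories explain part of the loss: with continuous items the 7/5/8 case is 60%, while 3 × 4 at 0.7 stays at 98%. With continuous items, 10 + 10 and 7 + 7 + 8 items at loading 0.7 gave 0%.

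**Would the later CFA show it?** Models with one factor too few were fitted to the population matrices (factor correlation 0.5) and compared with the plan's limit of a comparative fit index above 0.900:
- 4 + 4 + 4 at 0.7: 0.834
- 5 + 5 + 5 + 5 at 0.7: 0.875
- 7 + 9 + 6 at 0.6: 0.880
- 7 + 5 + 8 at 0.6: 0.888
- 8 + 6 + 3 at 0.7: 0.925, which passes

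The root mean square error of approximation in these models was 0.109, 0.074, 0.056, 0.056 and 0.064. Only the first breaches the plan's limit of 0.100.

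**The case against.** The strongest reply is that the plan does not stop at this rule. IRT tests the sets it produces, and CFA and IRT are repeated after six months and one year. In four of the five under-extracted models above, the comparative fit index would fail its limit. A reader might infer that an early error passes into every later validation result; the documents do not support that, because a merged factor would often appear as misfit. What remains is that the CFA is described as confirming the structure, no step sends the analysis back to extraction, the error-of-approximation limit would usually not flag the problem, and one of the five cases passes on both indices.

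Second, the loss is conditional. A reader might infer that the rule always drops real factors, or that TAS-20 and PUSH-D will lose dimensions. Neither follows. With long, strongly loading subscales the loss is nil. The article gives item counts for these two scales but no factor structure, and the new scales do not yet have items. Promax allows correlated factors; it does not imply a correlation of 0.5.

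Third, n = 317 applies a follow-up allowance to an analysis that comes earlier, and multiple imputation is planned. That is fair, but n = 396 hardly changes the results.

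Fourth, the authors may mean eigenvalues of the unreduced matrix, which would remove the mismatch. The text names principal-factor extraction and gives no such qualification. That reading has its own weakness: at n = 317 and loading 0.6, the unreduced rule kept too many factors in 14% of samples for 7/5/8 and 33% for 7/9/6.

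Expert and patient review before the factor analysis, and the earlier validation of the translated scales in other languages, give some protection. The plan does not link either to the number of factors.

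**Conclusion.** The concern holds in a conditional form. As written, the plan applies a full-matrix reference value to a reduced matrix, and the error runs towards too few factors. Its size ranges from none to nearly all samples across plausible structures. It is large for subscales of about 4–5 items, or for loadings near 0.6 with correlated factors, and absent for subscales of 6 or more items in the 7/9/6 pattern at 0.7. These figures rest on assumed structures and show what can happen; they do not predict the result for any named scale. The subscales, omega coefficients and CFA models of the new scales and of ItchyQoL, PUSH-D and TAS-20 may be misspecified or need rework. The rule should be changed, but the flaw does not invalidate the study.

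**What to change.** Replace the cut-off with parallel analysis on the reduced matrix: retain the leading factors whose eigenvalues exceed the 95th percentile of those from random data with the same n, item count and extraction. Check the result for interpretability and, for ItchyQoL, PUSH-D and TAS-20, against the published structure. Add that misfit in IRT or CFA leads back to extraction.

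If the authors did intend unreduced eigenvalues, they should say so; parallel analysis would still be the better rule.

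The cost is a sentence or two in the plan and one extra command, with no new data. The timing is good: at the article's status date of October 30, 2024, the new scales were still in item generation and 70 patients had joined.

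### The CFA fit limits are tied to maximum likelihood without saying whether fit statistics are scaled for skewed items; stating a scaled version is a cheap safeguard, not the correction of an error

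*Protocol article*

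**What the plan says.** Under Statistical analysis plan, the protocol article commits the follow-up factor analysis to a "CFA with a maximum likelihood estimation to reaffirm the scale structure". The limits are CFI above 0.900, SRMR below 0.100, RMSEA below 0.100, and a Tucker-Lewis limit printed as "non-normed fit index or Tucker-Lewis index (<0.900". That direction is taken here as a slip for above 0.900; it is a separate matter and no evidence for this point.

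The same section has item analysis cover the "normality of score distribution, including skewness and kurtosis tests". No sentence connects the result to how CFA fit is assessed. By contrast, other analyses may adapt to the data: Pearson or Spearman correlation as appropriate, and analysis of covariance or Kruskal-Wallis.

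The article neither plans nor excludes a robust correction. The section on Study I has dimensionality reaffirmed by CFA together with non-parametric IRT. Sample size estimation accepts 5 to 15 patients per question for CFA and sets a minimum of 396 patients, allowing for 20% missing responses.

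**The concern.** Questionnaire items with a few ordered answers are not normally distributed, and items on which most patients give the lowest answer are far from it. In that case the unscaled likelihood-ratio statistic is too large even when the factor structure is correct. CFI and TLI fall and RMSEA rises.

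The documents give no response formats or distributions for ItchyQoL, PUSH-D or TAS-20. One indirect hint concerns PUSH-D: Table 2 describes it as a tool for visible skin conditions, while Study population also admits patients with non-inflamed skin. Many of those patients might report no stigma.

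Validating the instruments is the first primary objective, and the CFA is part of its confirmation. A sound Thai version could appear to fit badly for a reason unrelated to its structure. If the choice between unscaled and scaled statistics is made only after fit has been seen, that choice is itself open to criticism.

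**Working it through.** **Sample size used.** The plan's 396 is reproduced by 22 items × 15 patients = 330, and 330 × 1.2 = 396. The 22 items are an assumption (top ItchyQoL score 110 ÷ 5 points per item). The correlation criterion alone (r = 0.30, 80% power, two-sided 0.05) needs only 85 patients, or 107 after dividing by 0.8, so it does not drive the total. Patients left after 20% loss: 396 × 0.8 = 316.8, about 317. At 5 per item, n = 17 × 5 = 85 or 22 × 5 = 110.

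**Formulas.** With model statistic T on df degrees of freedom and baseline statistic T_b on df_b:
- CFI = 1 − (T − df)/(T_b − df_b), with negative differences set to zero
- TLI = 1 − (T/df − 1)/(T_b/df_b − 1)
- RMSEA = √[(T − df)/(df(n − 1))]

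Satorra-Bentler scaling divides T by a factor c estimated from the items' fourth moments, and T_b by its own factor. Parameter estimates do not change.

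**Hand check.** For a correct model T averages about c × df, so unscaled RMSEA is about √[(c − 1)/(n − 1)]. With n − 1 = 316 and the simulated c for 17 items at loading 0.80:
- 50% floor, c = 1.42: √(0.42/316) = 0.036 (simulated 0.036)
- 70% floor, c = 1.93: √(0.93/316) = 0.054 (simulated 0.057)
- 85% floor, c = 3.10: √(2.10/316) = 0.082 (simulated 0.085)

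Reaching 0.100 would take c of about 1 + 316 × 0.01 = 4.16. Failures at this size therefore come mainly through CFI and TLI.

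**Simulation.** Correct models were fitted to items with 5 ordered categories: 17 items in one factor, and 22 items in three factors correlated 0.6. Loadings were 0.55, 0.70 and 0.80, with 150 data sets per cell and TLI read as above 0.900. The structures, loadings and category shares are assumptions. The table gives the share of correct scales that fail at least one limit, as a range over loadings and structures.

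| Answers in lowest category | n = 317, unscaled | n = 317, scaled | 5 per item, unscaled | 5 per item, scaled |
|---|---|---|---|---|
| symmetric items | 0% | nothing to remove | 0–22% | 0–23% |
| 50% on every item | 0% | nothing to remove | 5–76% | 0–40% |
| 10% to 70%, mixed | 0% | nothing to remove | 1–50% | 1–33% |
| 70% on every item | 0–41% | 0% | 85–99% | 3–58% |
| 85% on every item | 72–100% | 0–19% | 99–100% | 77–97% |

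At n = 317 with the 70% floor, the failures were 41% and 24% at loading 0.55 and at most 2% at 0.70 or above. With all 396 patients (60 data sets per cell), a 70% floor failed 0–17% and an 85% floor 33–100%.

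**Between those floors.** Separate runs of 17 items in one factor, n = 316 or 317, share missing CFI / TLI:
- 75% floor, loading 0.6: 28% / 47% in one run of 300 data sets and 25% / 39% in another; scaled 0% / 1% and 2% / 2%. This is an assumed severe-floor, moderate-loading case.
- 75% floor, loading 0.7: 5% / 14%; scaled 0% / 0%.
- 75% floor, loading 0.8: 0% / 1%.
- 80% floor, loading 0.70: 36% / 61%; scaled 0% / 0%.

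**Distortion without failure.** With a 50% floor, loading 0.80 and 17 items at n = 317, CFI averages 0.986 unscaled and 0.997 scaled, TLI 0.983 and 0.999, and RMSEA 0.036 and 0.011. Every data set passes, but the published indices look worse than they should.

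**The case against.** A reader might infer that the plan locks in uncorrected normal-theory statistics and is likely to reject valid scales. The documents support neither part. The text says only maximum likelihood, and scaled statistics are maximum likelihood with a rescaled test, so the stated method is compatible with the remedy. A condensed article may leave that option to the full plan. Strong floors are not documented for any instrument.

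The one relevant figure points towards strong loadings. Table 2 gives PUSH-D a Cronbach's α of 0.94 over 17 items. With equal items the mean inter-item correlation is 0.94/(17 − 16 × 0.94) = 0.94/1.96 = 0.48, so the observed loading is about √0.48 = 0.69. Simulated scales with a 75% floor and latent loading 0.6 reach a mean α of only 0.84. Latent loadings near 0.8 are needed for 0.94, and there CFI and TLI are missed in at most 0.3% and 1.7%. That α comes from another population, but it is the only one given.

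Three further points stand. The chi-square test is not among the plan's limits, so its inflation is not a failure under the plan. No rule says that a missed index leads to rejection or item removal, and non-parametric IRT runs beside the CFA. At 5 patients per item the small sample does part of the harm itself: symmetric items fail in up to 22%, and scaling does not repair that.

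What remains is that the article does name an estimator and numeric limits, and does not say what its own skewness checks are for in the CFA.

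**Conclusion.** The point holds as an inexpensive improvement, not as an error in the plan. At about 317 patients, wrong failures of the 0.900 limits are confined to two situations: floors of roughly 70–75% or more on all items with weak to moderate loadings, and floors near 80–85%. With symmetric items or a 50% floor they are essentially absent, and only the reported indices suffer a little at the 50% floor. Nearer 5 patients per item failures are more likely, but that would arise only if a CFA were run well short of the cohort target. Every size given rests on assumed loadings, category shares and factor structures. The documents do not show which of these cases applies to any of the scales.

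**What to change.** State under Statistical analysis plan that the CFA uses maximum likelihood with Satorra-Bentler scaled test statistics and robust standard errors, and that the CFI, TLI and RMSEA limits apply to the scaled values. SRMR can stay as it is. Optionally add that, where the planned skewness and kurtosis checks show strong floors, an ordinal (polychoric) estimator is run as a sensitivity analysis. Settle this before the follow-up CFA.

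The cost is one sentence and one option in the CFA command. The estimates do not change, and symmetric items show no material difference. The downside is that scaled indices are slightly less familiar to readers. Scaling does not replace an adequate sample: at 5 patients per item with a 70% floor, up to 58% of correct scales still fail.

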**Aspect of mental health, psychosocial, and psychosomatic symptoms**			
PHQ-9	Yes	Yes	• The PHQ-9 consists of 9 items to measure depressive symptoms (total score ranges from 0 to 27). • This scale showed excellent psychometric properties, with a Cronbach’s α of 0.90 among the general population in Thailand [29, 47]. • A cut-off point ≥9 was considered to indicate depressive symptoms [48].
GAD-7	Yes	Yes	• The GAD-7 consists of 7 items to measure anxiety symptoms (total score ranges from 0 to 21). • This scale had excellent psychometric properties, with a Cronbach’s α of 0.90 among the general population in Thailand [29, 47]. • A cut-off point ≥8 was considered to indicate depressive symptoms [49].
WHO-5 well-being index	Yes	Yes	• The WHO-5 well-being index consists of 5 items to measure health-related personal well-being. • This scale had excellent psychometric properties, with a Cronbach’s α of 0.91 among the general population in Thailand [29, 47]. • A cut-off point <50 was considered a low well-being index [47].
BRCS	Yes	Yes	• The BRCS consists of 4 items to measure cope tendencies with psychological stress (total score ranges from 4 to 20). • This scale had excellent psychometric properties, with a Cronbach’s α of 0.84 among the general population in Thailand [29].
TAS-20	Yes	No: translated and psychometric testing through this study	• The TAS-20 consists of 20 items to measure alexithymia (difficulty in identifying and describing emotions) [27]. • The non-Thai version showed adequate psychometric properties in 30 different languages (or dialects of the same language) [26].
PUSH-D	Yes	No: translated and psychometric testing through this study	• The PUSH-D is a dermatologic-specific scale to evaluate stigmatization in patients with visible skin conditions, which consists of 17 items [16]. • This scale demonstrated excellent psychometric properties, with Cronbach’s α 0.94 [16].
RSES	Yes	Yes	• The RSES consists of 10 items to measure self-esteem and is widely used in social science research. • The revised Thai RSES scale demonstrated excellent psychometric properties, with Cronbach’s α ranging from 0.84 to 0.86 [50].
UCLA Loneliness Scale-6	Yes	Yes	• The short version of the UCLA loneliness scale consists of 6 items to gauge loneliness levels. • This scale revealed acceptable psychometric properties in both non-clinical and clinical settings, with Cronbach’s α ranging from 0.72 to 0.84 [51].

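### The CFA criterion for the Tucker-Lewis index points the wrong way (<0.900), so a well-fitting structure cannot meet it and it nearly excludes the CFI criterion beside it

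*Protocol article*

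**What the plan says.** The Statistical analysis plan section of the protocol article states that during follow-up "we will perform a CFA with a maximum likelihood estimation to reaffirm the scale structure". It then names four fit indices, each with a cut-off in brackets:

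- "the comparative-fit index (>0.900"
- "non-normed fit index or Tucker-Lewis index (<0.900"
- "standardized root mean squared residual (<0.100"
- "root mean square error of approximation (<0.100"

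The section on Study I places this analysis after six months and one year of follow-up. It applies it to each multidimensional tool, alongside non-parametric item response theory. The article does not say whether the four criteria must hold together, and no other section restates or corrects the TLI cut-off.

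**The concern.** For the CFI, the SRMR and the RMSEA, the bracket gives the side on which fit is acceptable. For the TLI alone it gives the side on which fit is poor. The TLI and the CFI both increase with better fit, so one cannot sensibly be required above 0.900 and the other below it.

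The CFA is the step that confirms scale structure over time, under the first primary objective (psychometric validation). Read literally, the published criterion cannot be met by a sound structure. If the analysts quietly apply the opposite sign, the reported analysis departs from the published plan on a pre-stated threshold.

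**Working it through.** The cut-off is a decision criterion and not a computed figure, so there is nothing to reproduce. The check is on its direction and on its compatibility with the CFI cut-off.

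**Inputs.** The four cut-offs come from the Statistical analysis plan section. Item counts come from Table 2: PUSH-D, "which consists of 17 items"; "The TAS-20 consists of 20 items to measure alexithymia". Table 2 gives no item count for ItchyQoL; 22 is an assumption (top score 110, divided by an assumed 5 points per item). The factor counts of 1 and 3 are also assumptions.

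**Step 1: direction.** With b the baseline (null) model and m the fitted model:

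- CFI = 1 − (χ²m − df_m)/(χ²b − df_b)
- TLI = [(χ²b/df_b) − (χ²m/df_m)] / [(χ²b/df_b) − 1]

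TLI equals 1 when χ²m = df_m and falls as misfit grows. When χ²m ≥ df_m, rearranging gives

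1 − TLI = (1 − CFI) × df_b/df_m.

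The two indices therefore move together.

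**Step 2: values for one scale.** For p items and f correlated factors, each item loading on one factor, df_b = p(p−1)/2 and df_m = p(p+1)/2 − [2p + f(f−1)/2]. For 17 items and one factor, df_b = 136, df_m = 119 and the ratio is 1.143:

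| CFI | TLI | Meets TLI <0.900? |
|---|---|---|
| 0.99 | 0.989 | no |
| 0.95 | 0.943 | no |
| 0.85 | 0.829 | yes |
| 0.70 | 0.657 | yes |

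**Step 3: range in which CFI >0.900 and TLI <0.900 both hold.** The upper CFI limit is 1 − 0.1 × df_m/df_b.

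| Items, factors | df_b / df_m | Ratio | CFI range |
|---|---|---|---|
| 17, 1 | 136 / 119 | 1.143 | 0.900–0.9125 |
| 17, 3 | 136 / 116 | 1.172 | 0.900–0.9147 |
| 20, 1 | 190 / 170 | 1.118 | 0.900–0.9105 |
| 20, 3 | 190 / 167 | 1.138 | 0.900–0.9121 |
| 22 (assumed), 3 | 231 / 206 | 1.121 | 0.900–0.911 |

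The range widens for shorter scales: 10 items with one factor (45 / 35) gives 0.900–0.9222. The lengths of the new multidimensional scales are not yet known.

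**Step 4: simulation.** Maximum likelihood one-factor CFA, 17 items, N = 396 (the cohort target), 300 replicates, loadings of 0.7 assumed. The last three rows are two-factor data wrongly fitted as one factor.

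| True structure | Mean CFI | Mean TLI | Mean RMSEA | TLI <0.900 | CFI >0.900 and TLI <0.900 | CFI and TLI both >0.900 |
|---|---|---|---|---|---|---|
| One factor (correct model) | 0.998 | 1.000 | 0.008 | 0% | 0% | 100% |
| Two factors, r = 0.8 | 0.925 | 0.915 | 0.069 | 17% | 14% | 83% |
| Two factors, r = 0.5 | 0.726 | 0.687 | 0.129 | 100% | 0% | 0% |
| Two factors, r = 0.2 | 0.575 | 0.514 | 0.158 | 100% | 0% | 0% |

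The correct model never meets the criterion as written. The clearly wrong models always meet it, but their mean CFI and RMSEA lie on the wrong side of the cut-offs for those indices.

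**The case against.** The strongest reply is that this is a visible slip with little practical effect. The CFI cut-off in the same sentence shows the intended direction, and an analyst is unlikely to discard a model because its TLI is 0.97. That is probably right, and it limits the harm. It does not rescue the criterion, which is a stated threshold that nothing else in the article corrects.

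Three limits on the consequences also stand.

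- A reader might infer that poorly fitting structures would be accepted. That is true only of the TLI taken alone, which the article does not propose. If the indices are applied together, the CFI and RMSEA cut-offs stop clearly poor models.
- A reader might equally infer that good structures will be formally rejected. The article lists cut-offs without saying that all must hold, so that outcome depends on an all-must-hold reading.
- A reader might infer that every translated and new measure is affected. The Study I section confines the CFA to multidimensional tools. Several new measures in Table 2 are single items and cannot have a CFA. The exploratory factor analysis, item response theory, convergent and known-group validity, reliability and responsiveness analyses do not use this cut-off.

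**Conclusion.** The TLI criterion is wrong as written. This follows from the definition of the index and needs no assumption: a well-fitting structure has a TLI near 1 and cannot satisfy a requirement to lie below 0.900.

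The near-exclusion of the CFI criterion is also firm for scales of the length stated in Table 2. With 17 or 20 items and one or three factors, both hold only from CFI 0.900 up to between 0.9105 and 0.9147. The factor counts, the 22 items for ItchyQoL and the all-must-hold reading are assumptions. The item and factor counts move the upper limit only slightly; without the all-must-hold reading, the narrow range describes a conflict between two listed criteria and not a rejection rule.

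The reach is the six-month and one-year CFA of the multidimensional tools. The documents do not support a claim that poor scales would be validated, or that the psychometric programme as a whole is compromised.

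**What to change.** In the Statistical analysis plan section, change the non-normed fit/Tucker-Lewis criterion from <0.900 to >0.900, the same direction as the CFI. In the simulation above, the corrected TLI criterion is met by the correct one-factor model in 100% of samples and by the two clearly misspecified models (r = 0.5 and 0.2) in 0%.

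The cost is one symbol, with no effect on sample size, data collection or any other analysis. There is time: the Cohort status section reports 70 participants on October 30, 2024, with the new scales still at item generation, and the CFA belongs to follow-up. Make the change before the CFA is run and report it as an amendment, as the article undertakes to do.
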